### Recommendations:

The breakfast is may be the most difficult meal during the diet because we usually bread or bakery products due to his high energy level. So, eat fruit or dairy products like yogurts is very useful to overcome the diet. Also you can add nuts to your dairy products. Nuts are very energetic and they will help you to stand until lunch time.

Eat vegetables or salads with fish, meat or omelettes can be a good option for lunch or dinner.

Figure 3. Socio-demographic questionnaire for the volunteers. The questions ask for factors that could affect the excretion rate. They have to answer all the questions.

## Socio-demographic questionnaire

### Notes and instructions on completing the questionnaire:

This short questionnaire assesses some global affairs. We need this information to determine the results to interpret correctly. The information we collect in this questionnaire are only at for the purpose of scientific research into the metabolism and excretion of deoxynivalenol and its glucoside in humans and will be treated confidentially. This means that only the research team which is concerned with the study access to information and should not be passed to third person.

Moreover, everything is encrypted and you never mention your name. Please fill in this questionnaire them to bring along with your urine samples and give it away to one of our employees on a pre-arranged time.

Id number: .....

What is your date of birth? .....

What is your gender?

☐ Male

☐ Female

What is your height? .....cm

What is your weight? .....kg

Do you smoke cigarettes, cigars or a pipe?

☐ Yes

☐ No

Do you have a disease relating to ...?

- ☐ Liver
- ☐ Kidney
- ☐ Bile

What drugs and / or supplements you have taken the past month? What dose?

| Drugs / supplements | Doses |
|---------------------|-------|
|                     |       |
|                     |       |
|                     |       |
|                     |       |
|                     |       |
|                     |       |
|                     |       |
|                     |       |
|                     |       |
|                     |       |
|                     |       |

Are you pregnant or is there a chance that you are pregnant?

- ☐ Yes
- ☐ No

Breast-feeding?

- ☐ Yes
- ☐ No

Currently follow a diet where some foods should not be eaten because it of illness, allergy or for no reason?

- ☐ Gluten free
- ☐ Slimming free
- ☐ Diabetes
- ☐ Low salt
- ☐ Other.....

What diet do you follow?

- ☐ Western European
- ☐ Mediterranean
- ☐ Eastern
- ☐ Halal
- ☐ Kosher
- ☐ Low meat
- ☐ Vegetarian
- ☐ Vegan
- ☐ Other .....

Do you drink coffee every day? If so, how much?

- ☐ No
- ☐ Yes, I drink ..... cups of coffee per day.

Figure 4. Flow diagram with the timing assessments.

[figure not shown]

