### **Study Design**

**The scientific integrity of the study and the credibility of the study data depend substantially on the study design and methodology. The design of the study should include information on the type of study, the research population or the sampling frame, and who can take part (e.g. inclusion and exclusion criteria, withdrawal criteria etc.), and the expected duration of the study**

**(The same study can be described in several ways, and as complete a description of the study as possible should be provided. For example, a study may be described as being a basic science research, epidemiologic or social science research, it may also be described as observational or interventional; if observational, it may be either descriptive**

**or analytic, if analytic it could either be cross-sectional or longitudinal etc. If experimental, it may be described as a controlled or a non controlled study. The link below provides more information on how to describe a research study**

The human controlled intervention study is conducted according to the guidelines laid down in the declaration of Helsinki, and was approved by the Ethical Committee of the Ghent University Hospital (B670201630414). Participants, members of the research group and familiars, are contacted providing an invitation letter and can register for the study within two weeks after the call. All participants have to sign an informed consent. Each participant is informed on his/her right to withdraw from the study at any time and to consult a doctor immediately and inform us if they fell not right during the study but no adverse event are reported for any volunteers. Besides, no medical examinations or interventions are carried out in this study. The study is performed with 20 volunteers throughout an intervention and longitudinal trail, and recruited in Flanders (Belgium). All people older than 18 years old can take part in the study, less pregnant or breast-feeding women due to the potential risk to both mother and foetuses and persons with severe problems with liver, bile or kidney due to related risks for interferences with the mycotoxin metabolism. The volunteers are instructed to file a socio-demographic questionnaire involving details on age, gender, length, body weight, smoking, diseases, drugs or supplements, pregnancy, breast-feeding, diet and daily coffee consumption.

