The subjects have to follow a strict cereal-free diet during 3 days (Figure 1). Cereal-based foods and foods containing possible traces of wheat, rye, oats, maize and rice are restricted (*i.e.* bread and bread-based products, breakfast cereals, oat meal, muesli, cereal bars, waffles, cakes, (un)pealed rice, polenta, pizza, tortilla, pasta, popcorn, cereal-based chips, maize, beer, wine, pan meal and sauce-binders). The subjects are asked to detail their daily food intake through a questionnaire. On the third day in the morning, the subjects receive an oral bolus of DON or DON-3-glucoside based on the TDI ( $1\text{ }\mu\text{g/kg}$  body weight) and their body weight. The volunteers did the study twice: 1) DON administration and 2) DON-3-glucoside administration, between the two mycotoxin administration there are a washout period of two months. In addition, a control group of 4 volunteers follow the same protocol, however do not receive a bolus of DON or DON-3-glucoside after the cereal-free diet.

At day 3, volunteers have to collect a urine sample before the administration of the DON or DON-3-glucoside bolus (Figure 1). From the moment of administration, the 24-hours urine sample collection is requested. We deliver to each volunteer 12 containers (1L) to collect the urine. For every sampling point, time (hour of urine collection) and voided volume is recorded. All samples will be individually aliquotted to 20 mL, and stored in the freezer at  $-20^{\circ}\text{C}$  upon analysis. The samples are analysed with a Waters Acquity UPLC system coupled to a Quattro XEVO TQS mass spectrometer (Waters, Manchester, UK) was used to analyse the urine samples. Data acquisition and processing is performed with MassLynx™ version 4.1 and

QuanLynx® version 4.1 software (Waters, Manchester, UK). A Waters Acquity UPLC® HSS T3 (2.1 x 100 mm, 1.8 µm) column is applied (Waters, Manchester, UK).

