Volunteers have to be three days without eating cereals. It is difficult to control their diet for 24 h, so we absolutely trust in their free cereals diet. However, we know that if some volunteers do not follow the diet we will detect DON levels in the “blank” urine (the urine before toxin administration) and they have to repeat the intervention study. So, although we do not control totally the volunteers diet we have the “blank” urine as control of their good diet following. We deliver a list with the allowed and not allowed food to clarify even more the restricted food to the volunteers (Figure 2). On the other hand, we add four volunteers which will not take toxin administration but they do not know they are not taking the toxin administration just water. The 4 control volunteers will provide us information to compare the results. The control volunteers are random selected from the 20 volunteers. 2 males and 2 females will be randomly selected for control.

The volunteers have to answer a questionnaire where we ask for factors that could affect the toxin excretion (Figure 3). Moreover, we ask again about pregnant or breast feeding people as well as

kidney, liver or bile problems to be sure again that pregnant or breast feeding women and people with kidney, liver or bile problems are not included in the study.

Stickers with the code for each sample will be delivered to the volunteers with the urine collection containers. The volunteers have to stick each code to the urine sample and they have to add the hour of urine collection for each sample. This process is explained in detail to each volunteer when they come to collect the containers, moreover, we supply a completely detailed procedure about how to take the samples, where we added a phone number contact to call in case of doubts during the study.

Once, we received the samples from each volunteer we introduced the code, the hour and the volume for each sample in excel file and we take two aliquots of 20 mL for each samples and we stored until analysis in the freezer at -20 °C.

Then, the samples are analysed by LC-MS/MS with a previously validated method.

A flow diagram with timing assessments has been made with the study design and procedures (Figure 4).

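### The questionnaire used as a repeat eligibility check is handed in with the urine samples, too late to prevent the first bolus

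*Protocol*

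**What the plan says.** Under Study Design, the protocol admits adults, "less pregnant or breast-feeding women due to the potential risk to both mother and foetuses", and also excludes "persons with severe problems with liver, bile or kidney due to related risks for interferences with the mycotoxin metabolism". The Methodology says that the questionnaire asks about these conditions once more, "to be sure again that pregnant or breast feeding women and people with kidney, liver or bile problems are not included in the study".

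The form (Figure 3) gives the volunteer a different purpose and a return rule. The purpose is interpretation: "We need this information to determine the results to interpret correctly". The return rule is: "Please fill in this questionnaire them to bring along with your urine samples", at a time agreed beforehand.

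On timing, Study Design states: "On the third day in the morning, the subjects receive an oral bolus of DON or DON-3-glucoside". The 24-hour collection starts at administration, and the Urine Collection instructions place the last void on day 4. Each volunteer goes through the procedure twice, with a two-month washout. Study Design and Safety Considerations both say that no medical examinations are carried out.

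**The concern.** A check meant to keep people out of a study has to reach the staff before the exposure it guards against. Here the stated purpose and the stated return rule conflict: the form is a barrier to inclusion in the Methodology, but it travels with material that exists only after the toxin has been taken.

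The exclusion of pregnant and breast-feeding women rests on risk to mother and foetus, so it is a safety exclusion by the protocol's own account. If the instruction on the form is followed literally, a volunteer whose circumstances this check should catch would have taken the first bolus before anyone on the staff read her answer. No medical examination backs up self-report.

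**Working it through.** The protocol gives no figure to reproduce on this point. The check is one of sequence, followed by a simple count.

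**Sequence in one period**

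| Step | Time | Source |
|---|---|---|
| Pre-dose urine sample | Day 3, before the bolus | Study Design |
| Bolus | Day 3, morning (0 h) | Study Design |
| Last void | Day 4, about 24 h | Study Design; Urine Collection |
| Samples and questionnaire handed in | After the last void, so about 24 h or later | Form (Figure 3) |

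The time is approximate because Study Design starts the 24 hours at administration, while the volunteer instructions start them at the getting-up void that day. On either clock the samples are complete well after the bolus.

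**Sequence over both periods**

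- First bolus: the form arrives about 24 h later or more, and cannot prevent it.
- Second bolus: a form from the first round has been with the staff for about two months (the washout less about one day). It can prevent the second bolus, but its pregnancy answer is about two months old.
- If a new form is returned in each period, the second form again follows its bolus. The protocol does not say how often the form is completed. Under either arrangement this form gives staff no current answer before a bolus.

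**Count of first administrations**

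- The Methodology draws the 4 controls from the 20 volunteers: 20 − 4 = 16 first boluses.
- The Project summary and Study Design describe the controls as additional: 20 first boluses.
- The range is therefore 16 to 20.

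**Wording of the organ exclusion**

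- Study Design: severe problems.
- Methodology: problems, with no qualifier.
- Form: a disease relating to liver, kidney or bile.

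Someone reviewing a returned form would not know which standard applies to a ticked box.

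**The case against.** The strongest reply is that the form is not presented as the only barrier. The Methodology says that volunteers are asked 'again', which implies an earlier enquiry. Volunteers receive an invitation letter, register and sign consent. The consent pages were removed, and Figures 1 and 4 and the volunteer-instruction figure are not shown. This stands: nobody can say from these documents that there is no check before dosing. It does not reconcile the two passages, however, because the repeat check has its own stated purpose and its return rule defeats it. A missing figure showing earlier return would contradict the form's instruction, and reconciliation would still be needed.

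It can also be said that the form fixes when it is returned, not when it is filled in, so a volunteer might complete it before day 3 and recognise an exclusion. That is possible. But the form presents itself as an aid to interpretation and does not say that any answer is disqualifying, so self-withdrawal cannot be relied on.

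Four stronger readings are tempting and are not supported:

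- **That the form can exclude no one, or that all 32 to 40 boluses (16 × 2 to 20 × 2) escape it.** A form returned after the first round can bar someone from the second, or lead to removal from the analysis. Being too late for both would require return in the second period alone, which no passage says.
- **That ineligible people were dosed.** The count is of boluses that this check cannot precede. The protocol gives no basis for expecting any ineligible volunteer.
- **That the dosing weight arrives after dosing.** The form does ask "What is your weight? .....kg", but no passage says that the bolus is calculated from that entry. Body mass index is a regression covariate, which is reason enough to ask for height and weight.
- **That data from a pregnant or breast-feeding volunteer would distort the results.** Study Design gives interference with metabolism as the reason only for the liver, bile and kidney exclusion.

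**Conclusion.** The point holds in limited form. The Methodology and the instruction on the form contradict each other: a repeat eligibility check is returned too late to prevent the first of two administrations. It affects 16 to 20 planned first boluses, depending on the status of the controls. For the second bolus the check can act, but on a pregnancy answer about two months old if the form is completed once, in the first round.

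This rests on two assumptions. The first is that the urine samples named on the form are the completed set. The pre-dose sample is also urine, but no separate handover of it is described, and the Methodology logs samples once they have been received from the volunteer. The second is that the instruction is followed as printed.

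The point deserves correction because it concerns a safety exclusion and a stated rule that works against its stated purpose. The three wordings of the organ exclusion are a minor, separate inconsistency.

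**What to change.** 1. Change the instruction on the form and the matching text in the Methodology so that the questionnaire is completed, handed in and reviewed by staff when the volunteer collects the containers, before the first bolus.
2. State that the exclusion items are reconfirmed, and the answers seen by staff, before the second bolus.
3. Tell the volunteer on the form that these items bear on eligibility as well as on interpretation.
4. Reconcile the liver, bile and kidney exclusion across Study Design, Methodology and the form, so that one wording applies throughout. Which wording is for the sponsor to decide.
5. Because Duration of the Project describes sampling as already done, state when the forms were in fact received and reviewed relative to each bolus.

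The cost is a few sentences on the form and in the protocol, plus a brief reconfirmation before the second bolus. The first review needs no new visit, because the Methodology already has volunteers come in for the containers. No design feature, dose or analysis changes.

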### **Safety Considerations**

**The safety of research participants is foremost. Safety aspects of the research should always be kept in mind and information provided in the protocol on how the safety of research participants will be ensured. This can include procedures for recording and reporting adverse events and their follow-up, for example. It is useful to remember that even administering a research questionnaire can have adverse effects on individuals.**

The volunteers are cleared informed of the safety procedures followed during the study by letter. Moreover, each participant is informed on his/her right to withdraw from the study at any time and to consult a doctor immediately and inform us if they felt not right during the study. Besides, no medical examinations or interventions are carried out in this study and the toxins are administered with a water solution. Also we inform that we administered the TDI level of mycotoxin which cannot cause acute adverse effects.

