**Rationale & background information**

**The Rationale specifies the reasons for conducting the research in light of current knowledge. It should include a well documented statement of the need/problem that is the basis of the project, the cause of this problem and its possible solutions. It is the equivalent to the introduction in a research paper and it puts the proposal in context. It should answer the question of why and what: why the research needs to be done and what will be its relevance. The magnitude, frequency, affected geographical areas, ethnic**

**and gender considerations, etc of the problem should be followed by a brief description of the most relevant studies published on the subject.**

Deoxynivalenol (DON), also known as vomitoxin, is a mycotoxin that acts as a potent inhibitor of protein synthesis, stimulates the pro-inflammatory response, cause ribotoxic stress, cytotoxicity and apoptosis, resulting on the impairment of multiple physiological functions, such as the intestinal barrier, growth, immune regulation or reproduction. Furthermore, this mycotoxin has been linked with animal and human gastroenteritis outbreaks due to acute exposition (Pestka, 2010). Despite its toxicity, DON is a highly common mycotoxin in cereals and cereals products (([name], et al., 2012; Marin, Ramos, Cano-Sancho, & Sanchis, 2013) Marin et al., 2013) and as a result it is one of the major mycotoxins in our diets. Thus, exposition studies showed the large exposure of human to this toxin with high percentages of population exceeding the tolerable daily intake (TDI) (Heyndrickx, et al., 2015; Vidal, Cano-Sancho, Marin, Ramos, & Sanchis, 2016).

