## **Ethics**

**The protocol should have a description of ethical considerations relating to the study. This should not be limited to providing information on how or from whom the ethics approval will be taken, but this section should document the issues that are likely to raise ethical concerns. It should also describe how the investigator(s) plan to obtain informed consent from the research participants (the informed consent process).**

The study includes an administration of toxin, however, DON, the studied toxin, is a highly common mycotoxin in cereals. Even, several studies showed that a high percentage of population could exceed the tolerable daily intake of this mycotoxin (Heyndrickx et al., 2015; Vidal et al., 2016). Although acute exposure of animals to DON results in decreased feed consumption (anorexia), vomiting (emesis), abdominal pain, dizziness, headache, throat irritation, diarrhoea, and blood in stool (Rotter et al., 1996). While longer exposure causes reduced growth, and adverse effects on the thymus, spleen, heart, and liver (Sobrova et al., 2010). DON is not a carcinogenic mycotoxin as other mycotoxins like aflatoxins or ochratoxin A and The IARC classified DON in 1993 in Category 3, i.e., not classifiable as to its carcinogenicity to humans. So, although volunteers have to take a toxin administration they are three days without eating cereals which remove the DON exposure for three days. Besides, the DON administration is at TDI level (1 µg/kg/day) and The minimum emetic dose in pigs was 0.05 - 0.2 mg/kg b.w., when given orally.

To obtain the informed consent from the research participants we planned to explain carefully and in great detail all scientific data related to DON. Moreover, some participants are laboratory workers which have a better knowledge of mycotoxins.

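### Volunteers are told the bolus cannot cause acute adverse effects, but the protocol supports only a low expected risk, and adverse effects are captured by spontaneous report alone

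*Protocol*

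**What the plan says.** Protocol, Safety Considerations, on what volunteers are told: "Also we inform that we administered the TDI level of mycotoxin which cannot cause acute adverse effects". The same section informs them of their right "to consult a doctor immediately and inform us if they felt not right during the study", and says that no medical examinations are carried out.

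Protocol, Ethics, gives the grounds for the dose:
- The TDI, expressed per day: "the DON administration is at TDI level".
- Usual exposure: "several studies showed that a high percentage of population could exceed the tolerable daily intake of this mycotoxin".
- The diet: "they are three days without eating cereals which remove the DON exposure for three days".
- An animal threshold: "The minimum emetic dose in pigs was 0.05 - 0.2 mg/kg b.w., when given orally".

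The Ethics section also lists effects of acute exposure in animals, among them vomiting, abdominal pain, dizziness, headache and diarrhoea. Rationale & background information says of DON that "this mycotoxin has been linked with animal and human gastroenteritis outbreaks due to acute exposition", and gives no dose.

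Study Design repeats the instruction to see a doctor and inform the team, and adds: "no adverse event are reported for any volunteers".

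**The concern.** The assurance leaves no room for an acute effect. The evidence cited for it consists of a chronic daily limit, a population-exposure argument and an animal threshold. Each makes an acute effect at this dose less plausible, but none excludes one. The section also tells volunteers that acute effects cannot happen and asks them to act at once if they feel unwell, and these two messages pull in opposite directions.

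Two things are at stake. The first is the accuracy of what participants are told about a toxin given for research. The second is how the adverse-event statement can be read. If people hear that the bolus cannot make them ill, some may put nausea or headache down to the diet and not mention it. With spontaneous report as the only route described, an absence of reports says little about an absence of effects.

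**Working it through.** The Protocol states no safety margin, so there is no figure of its own to reproduce. The check has four steps.

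**1. Margin to the cited animal dose.**
- Dose given: 1 µg/kg body weight (Project summary, Study Design, Ethics).
- Oral emetic dose in pigs: 0.05 to 0.2 mg/kg (Ethics), which is 0.05 × 1000 = 50 µg/kg to 0.2 × 1000 = 200 µg/kg.
- Margin = animal dose / dose given: 50 / 1 = 50 and 200 / 1 = 200.

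The bolus is thus 50 to 200 times below the cited pig dose. That margin is large, but it comes from another species and from a single effect, emesis.

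**2. What each ground can support.**

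| Ground (Ethics) | Supports | Does not support |
|---|---|---|
| TDI of 1 µg/kg/day | the dose does not exceed a daily limit | a statement about a single bolus; no human single-dose figure is given |
| Many people may exceed the TDI by diet | intakes of this order are common | absence of acute effects, since none were measured in the text cited |
| Three cereal-free days | less DON from other sources | anything about the bolus itself |
| Pig emetic dose | a 50 to 200 fold margin | a human threshold, or effects other than emesis |

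**3. DON-3-glucoside.** Volunteers receive it in the second period, but the dose argument in Ethics concerns DON and cites no acute figure for the glucoside. The DON margin can be carried over only by assumption. Suppose 1 µg/kg is the mass of glucoside, all of it is hydrolysed to DON, and the glucoside has no acute effect of its own. With the Protocol's molecular weights (296 and 458 g/mole), the DON released is 1 × 296 / 458 = 0.646 µg/kg. The margin is then 50 / 0.646 = 77 to 200 / 0.646 = 309. On those assumptions the glucoside is no worse than DON, but the Protocol does not make the argument.

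**4. How an adverse effect would come to light.**
- Safety Considerations and Study Design: the volunteer informs the team and sees a doctor; no medical examinations.
- Methodology: a telephone number for doubts during the study.
- Socio-demographic questionnaire (Figure 3): no symptom item.
- Urine collection instructions: time, volume and containers go on a schedule; no symptom entry is mentioned.
- Follow-Up: instructions for the study only, with no follow-up of adverse events.

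Every route shown depends on the volunteer deciding to speak. Duration of the Project places sample collection from March to June and statistical analysis from July to the time of writing. The adverse-event statement in Study Design is therefore a remark made after the event, and it can mean no more than that nobody volunteered a complaint.

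**The case against.** The strongest reply is that the Protocol has more behind the dose than a pig study. It relies on the TDI, on ordinary diets that may exceed it, and on the removal of dietary DON. It also gives volunteers a clear route for reporting illness, repeats it, and supplies a telephone number. The study has no safety objective, so no estimate depends on the adverse-event statement. All of this stands. It limits the point to the wording of the assurance and the weight that the absence of reports can carry.

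A reader might infer several stronger things that the documents do not support:
- *That adverse effects probably went unreported.* Nothing shows this. The assurance may discourage reporting, and no more can be said.
- *That the Protocol claims no effects occurred, or prejudged the result.* It says none were reported, and the text was written after sampling.
- *That the background section contradicts the assurance outright.* The gastroenteritis outbreaks are cited without a dose, and the symptom list in Ethics refers to animals. Both sit uneasily with a categorical claim, but neither refutes it at 1 µg/kg.
- *That volunteers exceeded the TDI on the dosing day.* The bolus alone equals the daily TDI and Methodology concedes that diet is not fully controlled. However, no residual intake is given, and the documents do not show that exceeding the TDI causes acute effects.
- *That the sample is too small to prove safety.* This is true of any such study, but the Protocol does not offer its sample as proof of safety.

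The volunteers' letter, the consent pages, the instruction figure and the schedule form itself are not in the text available. They may hold further safety wording or a symptom field.

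**Conclusion.** The point holds as one of wording and ascertainment. The categorical assurance goes beyond the Protocol's own grounds. These amount to a low expected risk, with a 50 to 200 fold margin to a pig emetic dose for DON, no human single-dose figure and no acute figure for DON-3-glucoside. Because the reporting described is passive, the statement that no adverse event was reported is weak evidence of absence.

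The margin rests only on figures in the Protocol. The view on reporting rests on the text shown and would soften if the unseen letter or schedule asked about symptoms. The possible discouraging effect of the assurance is a judgement, and its size cannot be estimated from the documents. The excretion endpoints and their analysis are not affected. The correction is still worth making, because it concerns what participants are told and costs little.

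**What to change.** 1. Reconcile Safety Considerations with Ethics and with Rationale & background information. Replace *cannot* with *not expected*, and state the basis: the daily TDI, usual dietary intake, the 50 to 200 fold margin to the pig emetic dose, and the lack of a human single-dose figure. Say separately what the expectation for DON-3-glucoside rests on. Use the same wording in the volunteers' letter.
2. For any further dosing, add one yes/no symptom line to the schedule volunteers already complete for each urine sample, using effects named in Ethics (vomiting, abdominal pain, dizziness, headache, diarrhoea). Ask it in the same way of the water controls, who do not know that they receive no toxin, and report it for DON, DON-3-glucoside and control.
3. Move the adverse-event statement from Study Design to the results. For collections already finished, where a symptom line can no longer be added, word it as none spontaneously reported, unless it is documented that symptoms were asked about.

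The cost is a few sentences in the Protocol and letter and one line on a form. The downside is some nonspecific symptom reports. The four controls help to interpret these, though so few give only a rough comparison.
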